### Objective

The aim of this study is to evaluate inhibitory attentional control after 18 sessions of active LLLT and compare with the placebo group (sham LLLT). Our exploratory analysis will evaluate verbal and visuospatial episodic memory, executive functions (working memory, verbal and visuospatial fluency, attentional processes), and anxiety and depressive symptoms.

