
### Primary outcome

Inhibitory attentional control (time score) measured by Stroop test. The Stroop test is known to be an accurate assessment of executive function in mild to moderate TBI [52].

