### Sample size

Based on the previous pilot study [37] that analyzed the cognitive function of patients with TBI after repetitive sessions of RED/Near-infrared LED treatment. Considering the improvement on Stroop test of 1 standard deviation (SD) related to the baseline, the level of significance of 0.05 and the power of 80%, 16 patients per group was estimated. Considering the rate of 15% of drop-outs, we added two participants per group, ending with a total sample of 36.

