### Randomization

All eligible recruited patients will be randomly divided into two groups with a 1:1 ratio and blocks of four and six performed by the co-investigator through the randomization list (randomization.com). The randomization list will be kept in safe storage with the co-investigator responsible for the stimulation sessions. She will provide the allocation concealment assignment for the patients. No information about the assigned group will be given for the patient or to the research assessor.

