### Statistical analysis

Intention-to-treat and per-protocol analyses will be performed for the primary and secondary outcomes. Missing data will be analyzed with regression imputation, considering the confounders (months of the trauma, years of age, schooling years, and depressive symptoms). Patients that did not receive 60% of the total stimulation will be considered non-adherent and analyzed as per-protocol.

Means and standard deviation will be used to represent data with normal distribution and medians and quartiles to describe non-normally distributed data. Two-way ANOVA (2 groups × 3 times) with repeated measures (for parametric variables) or the Kruskal–Wallis test (for non-parametric variables) will be used for the analysis of the TLT effects obtained in the three timelines: baseline, one week, and three weeks after the intervention. The Bonferroni correction for multiple comparisons will be employed as a post-hoc test. The effect size will be calculated based on the difference between means of the pre-intervention and post-intervention evaluations and will be expressed with respective 95% confidence intervals. Parametric Student’s t-test or a Mann–Whitney *U* test for non-parametric data will be employed to assess between-group (active and sham helmet) differences in age, height, weight, and body mass index (BMI), time of TBI injury, level of education, and Glasgow Coma Scale at admission on the emergency room. For all effects, a *p* value < 0.05 will be considered indicative of statistical significance. The data will be organized and tabulated using the Statistical Package for the Social Sciences (SPSSv.19.0).

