## Discussion

The present study is designed to evaluate the effects of 18 sessions of LLLT over cognition, in patients with chronic moderate and severe TBI. Our primary hypothesis is that the sessions of active LLLT will improve attention (at least 1 SD) measured by Stroop test compared to the placebo group (sham LLLT). Our secondary hypothesis is that the active group will improve in all domains assessed by the neuropsychological battery, including cognition and mood, compared to placebo group.

LLLT can modulate many biological effects penetrating the scalp into the brain [25], playing a role improving the outcome of the patients in two different ways, depending on the stage of the trauma. In the acute phase after TBI, the initial neuronal injury occurs instantly and oftentimes causes irreversible damage to the central nervous system, due to impairment of neuronal cell functions, including mitochondria, and glia cells [18, 58]. The disruption of neuronal circuitry causes loss of connectivity between different areas of the brain and can negatively impact neural regeneration, leading to dysfunctional interactions. In the secondary stage after the trauma, other changes may occur, including release of neurotransmitters, decreased glucose utilization, lactic acid accumulation, reduced activity of ATP-reliant ion pumps, increased release of glutamate, Ca2 + −induced depolarization, and excitotoxicity [21, 58].

Previous studies showed improvement on cognition including attentional process and episodic memory after repetitive sessions of LLLT in patients with TBI [17, 37]. It seems that the LLLT decreases the inflammatory response, helping the neuroprotection after TBI. This process leads to increases on the ATP, cellular energy, and blood flow, decreasing the metabolic process. In summary, the LLLT seems to increase the intercellular synapses, acting as a possible treatment after acute and chronic TBI [37, 59–61].

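### The 2 × 3 ANOVA counts baseline as an outcome visit, and the plan does not name which effect or visit tests active against sham on the Stroop

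*Protocol article*

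**What the plan says.** The Objective is to "evaluate inhibitory attentional control after 18 sessions of active LLLT and compare with the placebo group". The Discussion gives the primary hypothesis as a between-group one: "sessions of active LLLT will improve attention (at least 1 SD) measured by Stroop test compared to the placebo group".

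The Primary outcome section reads "Inhibitory attentional control (time score) measured by Stroop test" and names no visit. The Neuropsychological assessment section describes Stroop interference as the extra time on Card 3 relative to Card 1.

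The Statistical analysis section specifies a "Two-way ANOVA (2 groups × 3 times) with repeated measures (for parametric variables", or a rank-based alternative. Baseline is listed among the three times. The decision rule is "For all effects, a *p* value < 0.05 will be considered indicative of statistical significance". Bonferroni is given as a post hoc correction.

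The Sample size section rests on a 1 SD improvement and states "the level of significance of 0.05 and the power of 80%, 16 patients per group was estimated".

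**The concern.** A 2 × 3 repeated-measures ANOVA gives three F-tests: group, time and group-by-time. Two of them, group and interaction, compare active with sham in some way. The article applies the same 0.05 threshold to all effects and does not say which one decides the primary hypothesis. It also does not say at which follow-up visit the arms are to be compared.

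Two things follow. If group or interaction may be chosen after the results are seen, the chance of a false claim is higher than 5%. And the group main effect averages over baseline, where randomised arms cannot differ because of treatment, so it is a weak test of the hypothesis. With 36 patients, one primary claim should rest on one named test that uses the baseline score well.

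**Working it through.** **Inputs from the article.** Effect 1 SD, significance level 0.05, power 80%, 16 per group before drop-outs (Sample size); 1:1 allocation (Randomization); three assessments including baseline (Statistical analysis).

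**Assumptions, not in the article.** Two-sided testing, normal data, SD 1 at each visit, and correlation ρ between visits from 0.3 to 0.8, equal for all pairs of visits unless noted.

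**1. The plan's own figure.** The two-group formula n = 2(z₀.₉₇₅ + z₀.₈₀)²·(SD/δ)² with δ = SD gives 2 × (1.960 + 0.842)² = 15.7, so 16 per group. The stated figure is reproduced by a simple comparison of two means, not by an ANOVA effect. An exact t-test with 16 per group has 78.1% power.

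**2. False claims under no treatment effect.** Taking the two tests as roughly independent, the chance that group or interaction reaches p < 0.05 is 1 − 0.95² = 9.75%. Simulation (20,000 runs, 16 per arm) gives 9.9% at ρ = 0.5 and 9.8% at ρ = 0.7. A separate simulation with 15 per arm (3,000 runs) gives 9.0%. A single baseline-adjusted test gives 5.0%.

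**3. Dilution of the group effect.** For arm differences of 0, 1 and 1 SD at the three visits, the group effect is (0 + 1 + 1)/3 = 2/3 SD. The variance of a patient's three-visit mean is (1 + 2ρ)/3, so the standardised effect is (2/3)/√((1 + 2ρ)/3). This is 0.91 at ρ = 0.3 and 0.72 at ρ = 0.8, which with 16 per arm gives power of 70.5% and 50.0%, in agreement with the simulation below.

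**4. Power for a sustained 1 SD effect, 16 per arm (simulation, %).**

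| ρ | Group effect | Interaction | One-week ANCOVA |
|---|---|---|---|
| 0.3 | 70.6 | 67.5 | 80.7 |
| 0.5 | 61.0 | 82.5 | 87.2 |
| 0.6 | 57.1 | 89.9 | 91.7 |
| 0.7 | 53.0 | 96.5 | 96.3 |
| 0.8 | 49.8 | 99.7 | 99.4 |

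As a check on the interaction column, the noncentrality is n/(3(1 − ρ)). At ρ = 0.5 this is 16/1.5 = 10.67 on 2 and 60 df, which gives 82.1%.

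**5. Other patterns: one-week ANCOVA against interaction (simulation, %).**

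| Pattern | ρ = 0.5 | ρ = 0.7 |
|---|---|---|
| Effect halves by the last visit | 87.3 vs 69.0 | 96.3 vs 90.0 |
| Effect gone by the last visit | 87.7 vs 82.1 | 96.4 vs 96.6 |
| Sustained effect, correlation decaying over time | 87.4 vs 73.9 | 96.3 vs 90.3 |
| Effect grows from 0.5 to 1 SD | 34.7 vs 69.4 | 46.9 vs 90.0 |

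**The case against.** The usual reading of such an ANOVA takes the group-by-time interaction as the test of interest. If that term were named, it would be a valid 5% test. With 16 per arm and a sustained effect it exceeds the planned 80% power from ρ = 0.5 upwards. Choosing the model term is also something a statistical analysis plan often settles, and that document is not shown. These points stand in part. The plan is not shown to lack power, and ANCOVA is not better in every case. But the article itself fixes the model, the role of baseline and the threshold, and as written they leave the primary test open.

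A reader might infer that any significant effect, including a time effect from practice or placebo response, would count as success. The documents do not support that. The rule for all effects sets a significance threshold, not a criterion for trial success. The Objective and the Discussion state a comparison with sham, which a time effect cannot satisfy. So the roughly 14% chance (1 − 0.95³) that at least one of the three effects is significant does not measure the trial's error rate.

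A reader might also infer that a one-week baseline-adjusted test is always more powerful. It beats the group effect at every correlation examined. Against the interaction, the answer depends on the correlation and on the course of the effect, and the article gives neither.

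The Bonferroni correction is the plan's multiplicity provision. It governs post hoc comparisons and does not say which omnibus effect is primary.

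**Conclusion.** The point holds as a defect of specification with a better method available at no cost. Neither an effect nor a visit is designated for the primary hypothesis. If group or interaction may be claimed, the error is about 9–10% rather than 5%. If the group effect were used, a sustained 1 SD difference shrinks to 2/3 SD and power falls to about 71% at ρ = 0.3 and 50% at ρ = 0.8.

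Compared with a named interaction, the one-week baseline-adjusted contrast gains about 13, 5 and 2 points at ρ = 0.3, 0.5 and 0.6 for a sustained effect, and more if the effect halves at ρ = 0.5 or 0.7. It is about equal at 0.7 to 0.8. It loses about 35 to 43 points if the effect builds from 0.5 to 1 SD after one week. All power figures rest on the assumed correlations, normal data and 16 evaluable patients per arm.

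**What to change.** Before unblinding, state one primary analysis: active against sham on Stroop interference time (Card 3 minus Card 1) at one follow-up visit designated by the sponsor, by ANCOVA or the corresponding mixed-model contrast, with the baseline Stroop score as covariate, two-sided 5%. One week fits the Objective's wording about the period after 18 sessions, but the article does not fix the visit. The sponsor should weigh whether the effect is expected early or late.

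Make the other follow-up visit secondary. State that neither the time nor the group main effect will be taken as evidence of a treatment effect.

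Reconcile the timing of the last assessment: the Statistical analysis section puts it three weeks after the intervention, while the Abstract and the Neuropsychological assessment section put it at three months.

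The cost is wording only. The baseline Stroop score is already scheduled, and no extra patients or visits are needed.

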#### Neuropsychological assessment

Patients will be assessed at baseline, one week after the end of the LLLT, and three months after the LLLT sessions. Each patient will follow the participation period as shown in Fig. 1.

Instruments:Beck Depression Inventory (BDI-II), used to assess depressive symptoms, classified as minimal (0–11 scores), mild (12–19), moderate (20–35), and severe (36–63) [41, 42];Beck Anxiety Inventory (BAI), used to assess anxiety symptoms, classified as minimal (0–7 scores), mild (8–15), moderate (16–25), and severe (26–63) [42];Trail Making Test A and B (TMT A and TMT B), used to measure attention, speed, and mental flexibility. In TMT A, the patient is instructed to draw a line from 1 to 2, 2 to 3, and so on. In TMT B, the patient switches between numbers and letters, drawing a line from 1 to A, A to 2, 2 to B, and so on. On both forms A and B, the patients perform a sample before the real test. The patient is instructed to perform as fast as he/she can [43];Stroop Test - Version Victoria, measuring cognitive control with each person can maintain a goal in mind and suppress a habitual response in favor of a less familiar one. The interference effect is determining by calculating the extra time required to name colors (Card 3) in comparison to the time required to name colors in the control task (Card 1) [43, 44];Controlled Oral Word Association Test (COWAT), used to evaluate the spontaneous production of words under restricted search conditions (verbal association fluency). For the phonemic fluency task, the patient must provide orally as many words as possible beginning with the letters F, A, and S for 1 min for each letter. For the semantic fluency task, the patient is asked to produce as many animals’ names as possible within 1 min. The total correct is the sum of all admissible words for the semantic category [43];Five-point test, this test requires preproduction of novel designs under time constraints (3 min). The score is calculated including the total number of unique designs and the number of repeated designs (perseverations) [45];Symbol Digit Modalities Test (SDMT) oral version, the test is used to assess divided attention, visual scanning, tracking, and speed. The examiner records the numbers that correspond with symbols. The number of correct substitutions within the 90-s interval is the score of the task [46, 47];Rey Auditory Verbal Learning Test (RAVLT), measures immediate episodic memory, learning, susceptibility to interference, and recognition memory. A list of 15 nouns (list A) is read aloud to the patient, for five consecutive trials, each followed by a free-recall test. An interference list of 15 words (list B) is presented, followed by a free-recall test of that list. Immediately after this, delayed recall of list A is tested (Trial 6), and after 20 min (Trial 7), without further presentation of those words. The recognition is performed by presenting 50 words containing words from lists A, B, and new words, and the patient needs to identity the words from list A [43, 48];Sequence Numbers and Letters (Wechsler subscale - WAIS-III), used to evaluate working memory, random numbers, and letters is presented orally to the patient and must be mentally organized and immediately reported to the examiner with the following rule: first the crescent numbers then the letters (in alphabetical order). In test difficulty increases the patients correctly perform the task [49];Digit Span (DS) Forward and Backwards (WAIS-III), the DS assesses working memory. For the DS forward, the patient hears carefully a sequence of numbers and must repeat it immediately in the same sequence as previously presented. For the DS backwards, the patient must repeat the sequence inversely. In both conditions the number of numbers presented increases as the patient hits two corrects scores from the same span [49];Rey-Osterrieth Complex Figure Test (ROCF), the purpose is to assess visual–spatial constructional ability and visual memory. The patient is required to copy the ROCF, and after 3 and 30 min, a white sheet is given to the patient, and asked to draw the amount of information retained over time [50, 51].

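### Kruskal–Wallis is named as the rank-based substitute for the 2 groups × 3 times repeated-measures ANOVA, but over three repeated assessments it does not give a valid active-versus-sham comparison

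*Protocol article*

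**What the plan says.** The protocol article's Statistical analysis section gives the efficacy analysis in one sentence with two branches. The first is "Two-way ANOVA (2 groups × 3 times) with repeated measures (for parametric variables"). The second, in the same sentence and for the same purpose, is "or the Kruskal–Wallis test (for non-parametric variables) will be used for the analysis of the TLT effects", over the three time points. Bonferroni is named for post-hoc multiple comparisons.

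The measurements come from the same people each time. Under Neuropsychological assessment: "Patients will be assessed at baseline, one week after the end of the LLLT, and three months after the LLLT sessions".

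The primary outcome is "Inhibitory attentional control (time score) measured by Stroop test". The Discussion states the primary hypothesis as a contrast between arms: "active LLLT will improve attention (at least 1 SD) measured by Stroop test compared to the placebo group (sham LLLT").

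A rank test for two arms does appear in the Statistical analysis section, but only for baseline characteristics: "Mann–Whitney *U* test for non-parametric data will be employed to assess between-group (active and sham helmet) differences in age, height, weight", and the further characteristics listed there. No other rank-based efficacy analysis is named.

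**The concern.** The two branches are presented as alternatives for one question, but they do not answer the same question. The ANOVA has a within-patient factor and a group-by-time interaction, and the interaction carries the treatment effect. Kruskal–Wallis has neither. It asks whether several independent samples share one distribution.

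The cognitive battery is given three times, so some gain from repetition in both arms is plausible. Separating that gain from treatment is the purpose of the sham arm. If a variable goes down the non-parametric branch and the test is run over the time points as worded, the comparison with sham is lost or is made at the wrong error rate. The branch is open to any outcome judged non-normal, including the primary one.

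**Working it through.** **Inputs from the protocol article.** Three assessments per patient; 1:1 allocation; 16 per group, raised to 18 per group (36 in total) for dropout; alpha 0.05 (sidedness not stated, two-sided assumed); target effect 1 SD (Sample size: "Considering the improvement on Stroop test of 1 standard deviation (SD) related to the baseline").

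**Inputs not in the article, assumed.** Within-patient correlation 0.5–0.8, equal between all pairs of visits; normal data; a practice gain of 0.5 SD, the same in both arms and present in full at both follow-ups.

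**The plan's own figure.** For two independent means, n per group = 2 × (1.96 + 0.84)² × (SD/difference)² = 2 × 7.84 × 1 = 15.7, so 16. This reproduces the stated 16. It is the formula for a comparison between arms. The sample size is not affected by the present point.

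**The possible uses of Kruskal–Wallis.** The text does not say what defines the groups. There are four candidates.

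1. *Three time points as groups, arms pooled.* Three records of one patient count as three patients, and arm does not enter.
2. *Two arms as groups, all three visits stacked.* Each patient counts three times. With correlation ρ, the variance of an arm's average is 1 + 2ρ times what the test assumes, so the approximate rejection rate with no effect is 2 × [1 − Φ(1.96/√(1 + 2ρ))]:
   - ρ = 0.5: 1.96/√2.0 = 1.386, giving 0.166
   - ρ = 0.6: 1.96/√2.2 = 1.321, giving 0.186
   - ρ = 0.8: 1.96/√2.6 = 1.216, giving 0.224
3. *Six arm-by-time cells as groups.* A change over time shared by both arms makes the cells differ, so rejection does not point to treatment.
4. *Two arms as groups, at one visit or on change from baseline.* Each patient contributes one value, so the test is valid. With two groups it is the Mann–Whitney test (in one check both gave p = 0.04288).

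**Simulated rejection rates at nominal 5%** (18 per arm, normal data, ρ 0.5–0.8):

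| Use | Nothing changes | Equal 0.5 SD practice gain, no treatment effect | True 1 SD treatment effect, no practice |
|---|---|---|---|
| 1. Over times, arms pooled | 0–0.5% | about 48–54% | about 35–40% |
| 2. Arms, visits stacked | 17–23% | – | – |
| 3. Six cells | – | 26–31% | – |
| 4. Arms, one visit or change | about 4–7% | about 4–7% | 81% (one visit), 88% (change), at ρ = 0.6 |

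Use 1 is more likely to reject for shared practice than for a real treatment effect twice as large.

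**Sensitivity.** The shape of the practice gain matters. At ρ = 0.6, a gain of 0.5 SD in total gives 52% under use 1 if it is a step at both follow-ups, but 33% if it builds up linearly.

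Right-skewed (log-normal) data with ρ 0.5–0.9 and a shared 1 SD trend give the same picture. Use 1 rejects in 99.9–100% and use 3 in 99–100% with no treatment effect. Use 2 rejects in 16–24% with no effect at all. Use 4 at a single visit stays at 4.8–5.4%.

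**The alternative.** Mann–Whitney on change from baseline at the first follow-up rejected in 4.0–5.3% of normal-data trials without a treatment effect, with or without practice. Its power for 1 SD was 81–99%. On the log-normal data its level was 4.3–4.9% and its power 65%, 84% and 99.7% at ρ = 0.5, 0.7 and 0.9. These power figures are at 0.05 for one visit, before any Bonferroni adjustment.

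**The case against.** The strongest reply is that Kruskal–Wallis can be used properly here. Between arms at each visit, or on change scores, it keeps its level and tests active against sham. So a reader who infers that the test cannot compare the arms goes too far. What stands against the reply is the wording. The sentence makes the test a substitute for the 2 × 3 repeated-measures analysis over the three time points, and neither the single-visit nor the change-score use is stated.

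The second reply is that this is only a fallback. That is correct: the lead analysis is the ANOVA. A reader might infer that the primary analysis will take the rank-based branch because times tend to be skewed. The article gives no distribution for the Stroop score, and under Neuropsychological assessment the interference effect is a difference between two times. All that can be said is that the primary outcome is not exempt.

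Third, the simulated rates rest on a correlation and a practice gain that the article does not give. This limits the figures, but not the reasoning about independence and the missing interaction.

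Fourth, an analysis plan that is not shown may set out the implementation. That would excuse a missing detail. Here, however, a test is named, and as named it does not fit the design.

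**Conclusion.** The point holds as a wrong method for the stated use. Over three repeated assessments, Kruskal–Wallis either leaves arm out, treats correlated records as independent, or cannot separate time from treatment. It becomes a valid between-arm test only in a form that the plan does not describe. The problem is confined to outcomes judged non-normal, from which the primary outcome is not excluded.

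The rates are illustrations under the assumptions listed. In particular, the figure of about 48–54% is not this trial's false-positive rate. It is the chance that a test of time alone is significant when both arms improve equally, and it would become a false treatment claim only if someone read that result as active versus sham. The documents do not say that they would.

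Two further inferences are also unsupported. The article does not say how, when or by whom normality will be judged, so it cannot be said that the test will be chosen on unblinded data. It also names no primary time point, so no visit should be treated as primary here.

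**What to change.** In the Statistical analysis section, replace Kruskal–Wallis for the efficacy outcomes with a rank-based comparison between arms that uses baseline, at each follow-up visit. Either rank ANCOVA of the follow-up score on baseline or Mann–Whitney on change from baseline will do; name one. Carry the existing Bonferroni correction across the visits: with two follow-ups, 0.05/2 = 0.025 each. State before unblinding which outcomes, including the Stroop score, are analysed this way.

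The cost is a change of wording and a few lines of code, with no new data and no change to the sample size calculation. Power at 0.025 per visit will be somewhat lower than the single-visit figures above.

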### Rationale for the photobiomodulation using low-level laser therapy (LLLT) in patients with TBI

Considerable evidence has shown that the brain has an extensive ability of reorganization after damage [18]. Non-invasive brain stimulation (NIBS) can modulate brain plasticity after trauma through increasing synaptic strength, modulating neurotransmitters, and modifying neural networks [18–21]. LLLT is a technique of NIBS that the irradiation of specific infrared wavelengths is able to penetrate deeply into the brain [22]. These effects produce many biological responses, such as affecting the forming of adenosine triphosphate (ATP), increasing deoxyribonucleic acid (DNA) and ribonucleic acid (RNA), releasing nitric oxide (NO), cytochrome c oxidase (CCO), regulating reactive oxygen species (ROS), and modifying intracellular organelle membrane activity particularly in mitochondria, calcium flux, and stress proteins [23–25]. LLLT produces a shift toward higher oxidation in the overall cell redox potential [26] and briefly increases the level of ROS [27]. This change in the redox state of the mitochondria regulates several transcription factors [28]. These include redox factor-1 (Ref-1), cAMP response element (CREB), activator protein 1 (AP-1), p53, nuclear factor kappa B (NF-jB), hypoxia-inducible factor (HIF-1), and HIF-like factor [28]. The activation and regulation of redox-sensitive genes and transcription factors are thought to be caused by ROS induced from LLLT [27]. In turn, both ATP levels and blood flow increase, improving oxygenation found in damaged areas of the brain [28]. In animal models, LLLT has been investigated as an alternative treatment for brain injury, increasing neurogenesis after TBI [29] and showing a protective effect for stroke [30] and benefits for acute ischemic stroke, acute myocardial infarction, injured peripheral nerves, and spinal cord injury [31–33]. Previous studies showed the safety of photobiostimulation in humans [34], including promising interventions for acute stroke [34], TBI [17, 35–37], and dementia [38]. However, to date, just one open-label clinical trial studies the effect of LED therapy on improving cognitive function in patients with TBI [37]. Likewise, no randomized controlled trial studied the short-term and long-term effects of LLLT on the cognition of closed TBI patients.

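### The reported effect size names no active-versus-sham contrast, and the 1 SD used for planning is worded as a gain on baseline but computed as a difference between arms

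*Protocol article*

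**What the plan says.** The Objective section of the protocol article sets a comparison with sham: "The aim of this study is to evaluate inhibitory attentional control after 18 sessions of active LLLT and compare with the placebo group (sham LLLT". The primary outcome is "Inhibitory attentional control (time score) measured by Stroop test". The Discussion gives the primary hypothesis, that "the sessions of active LLLT will improve attention (at least 1 SD) measured by Stroop test compared to the placebo group".

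For estimation, the Statistical analysis section says: "The effect size will be calculated based on the difference between means of the pre-intervention and post-intervention evaluations", with 95% confidence intervals. No comparison of arms is attached. The same section plans a repeated-measures ANOVA with two groups and three times for parametric variables. It mentions between-group t or Mann–Whitney tests only for demographic, anthropometric and injury characteristics.

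The Sample size section starts from a pilot: "Based on the previous pilot study [37] that analyzed the cognitive function of patients with TBI after repetitive sessions of RED/Near-infrared LED treatment". It continues: "Considering the improvement on Stroop test of 1 standard deviation (SD) related to the baseline", and then "the level of significance of 0.05 and the power of 80%, 16 patients per group was estimated". Two per group are added for drop-out, which makes 36. On that same reference, the Rationale section says that "just one open-label clinical trial studies the effect of LED therapy on improving cognitive function in patients with TBI [37".

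**The concern.** A pre-to-post difference in a trial arm is the sum of the treatment effect and everything else that changes between two Stroop tests: practice (the test is scheduled three times), placebo response and regression to the mean. The sham arm is there to subtract those parts. An effect size that is not contrasted with sham keeps them in, and its interval can exclude zero when active and sham do equally well.

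The planning effect raises the same question. An improvement on baseline and an advantage over sham are different quantities, and they are equal only if sham patients do not change. The Sample size section describes the former and the Discussion the latter, for the same 1 SD. At stake are whether the published estimate answers the trial's question and how far the stated 80% power can be relied on.

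**Working it through.** **Inputs from the article.** Effect 1 SD, significance level 0.05, power 80%, 16 per group, 18 per group after the drop-out allowance, 1:1 allocation. Sidedness is not stated.

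**Inputs assumed here, because the article gives none.** Gain under sham (practice plus placebo) s = 0.3 to 0.5 SD; pre-post correlation ρ = 0.6; equal SDs before and after.

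**Step 1. Reproduce the plan's 16.** For two arms and a between-arm difference Δ, n per arm = 2(z₀.₉₇₅ + z₀.₈₀)²σ²/Δ². With Δ = σ this is 2 × (1.960 + 0.842)² = 15.7, so 16. The t-test version gives 16.7, so 17. A one-sided test gives 13 by the normal formula.

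For a 1 SD change tested within one arm, n = (1.960 + 0.842)² = 7.85, so 8, or 9.9, so 10, with a paired t-test.

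Of these, only the two-sided, two-sample calculation gives 16. The arithmetic therefore treats 1 SD as active minus sham, although the sentence describes it as relative to baseline.

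**Step 2. What follows if 1 SD is a gain on baseline.** The between-arm difference is then 1 − s. Power of a two-sided two-sample t-test with 16 per arm uses d = (1 − s)/SD, where SD depends on the analysis:
- post-treatment score, or any analysed score with SD 1: SD = 1
- change score: SD = √(2(1 − ρ)) = √0.8 = 0.894
- baseline-adjusted score: SD = √(1 − ρ²) = √0.64 = 0.8

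| Sham gain s | Difference | SD 1 | Change score, ρ = 0.6 | Baseline-adjusted, ρ = 0.6 |
|---|---|---|---|---|
| 0 | 1.0 | 78% | 86% | 93% |
| 0.3 | 0.7 | 48% | 57% | 67% |
| 0.5 | 0.5 | 28% | 33% | 40% |

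If all 18 per arm are analysed (N = 36), the same formula gives, for differences of 0.7 and 0.5 SD, 53% and 31% (SD 1), 63% and 37% (change score), and 72% and 45% (adjusted).

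The result is sensitive to ρ. At ρ = 0.8 the change-score power with 16 per arm (normal approximation) is 88% for 0.7 SD and 61% for 0.5 SD.

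**Step 3. What a pre-post interval shows when treatment does nothing.** Take one arm of 18, a gain of 0.3 or 0.5 SD from practice and placebo alone, and ρ = 0.6. The standardised change is 0.3/0.894 = 0.335 or 0.5/0.894 = 0.559. The paired t-test power, which is the chance that the 95% interval excludes zero, is 27% or 61%.

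**The case against.** The strongest reply is that the article does plan a comparison of arms. The 2 × 3 ANOVA contains a group-by-time term that tests active against sham for parametric data, the effect-size sentence comes shortly after it, and the article frames the question as active versus sham throughout. An effect size based on pre-post differences could still be contrasted between arms afterwards. Much of this stands. A reader might infer that the trial has no between-arm test, or that the 27–61% in step 3 is its false-positive rate; the article supports neither. That figure concerns one arm's interval, not the ANOVA. What does not stand is that the ANOVA settles the estimate. The sentence defines the effect size and its interval without naming the arms, and the group-by-time term is not named either.

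On planning, the reply is that the Discussion states 1 SD against sham and that 16 per group is correct for that target. This is fair as arithmetic. It leaves the two sections giving one number two meanings. A reader might go further and call the pilot uncontrolled and the 1 SD its within-arm result. The article says only open-label and does not say that 1 SD is what the pilot observed, so both remain inferences.

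A reader might also conclude that 80% power needs sham patients not to improve at all. That is too strong. At ρ = 0.6 and 16 per arm, 80% power needs a difference of about 0.92 SD with change scores or 0.82 SD with baseline adjustment, so a sham gain of about 0.08 or 0.18 SD could be absorbed, and more with a higher correlation.

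**Conclusion.** The point holds in two limited parts. First, the effect size and interval as written do not isolate active versus sham, although that is the aim and the primary hypothesis. This follows from the text and needs no assumption. Second, the planning effect is worded as an improvement on baseline and calculated as a difference between arms. If the first meaning is intended, the calculation assumes no change under sham.

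The size of the second part is illustrative. With a sham gain of 0.3–0.5 SD and 16 per arm, power lies between about 67% and 28%, depending on the gain and on the analysis, for a correlation of 0.6 or an analysed-score SD of 1. The article gives neither the sham change nor the correlation, and at a correlation of 0.8 the smaller gain would leave power above 80%. The conflict between the sections is certain; the loss of power is conditional.

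**What to change.** 1. **Statistical analysis.** Define the effect size as the active-minus-sham difference in Stroop time score, adjusted for baseline, with its 95% confidence interval, standardised by the pooled baseline SD. Give it at one week and at the later follow-up. Name the group-by-time contrast as the test of active versus sham. Keep within-arm changes as description only.
2. **Sample size and Discussion.** Reconcile the two statements. Say that 1 SD is an assumed between-arm difference and that the pilot was open-label, so it does not itself supply an active-minus-sham figure. Give the power of N = 36 for smaller differences such as 0.7 and 0.5 SD, with the correlation assumed.

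The cost is wording only, with no extra patients or visits. The drawback is that the stated power will look less favourable. The first change should be settled before unblinding, because it governs the reported estimate for the primary outcome.
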